## Methods

### Design plan

We will conduct a non-randomized mixed-methods pilot and feasibility study in which all participants will receive the FoRSHE-X intervention. We will adapt the RE-AIM Framework of O’Brien and colleagues [22] to evaluate the feasibility and pilot study (Table 1). The RE-AIM dimensions represent multiple tasks of complex multi-component intervention [22]. This feasibility study asks questions: Can a definitive trial to assess the effect of an intervention be conducted? Should we proceed with it, and how? [23]. A pilot study is a subset of a feasibility study in which the future trial is entirely or partially performed on a smaller scale [23]. Quantitative and qualitative approaches will be used to achieve the study objectives.

**Table 1 pone.0299901.t001:** Defining objectives and data collection using RE-AIM framework.

RE-AIM Dimension	Objectives	Quantitative Data	Qualitative Data
**Reach**	To examine the eligibility and acceptability of the participants.	Demographic and clinical data	Participants’ experience and perspective on the acceptability of the recruitment process and involvement in this study.
		Acceptance of the research invitation	Facilitators’ concerns and challenges in recruiting potential participants.
**Effectiveness**	To evaluate the impact of the intervention outcomes.	Chemotherapy side effects	Participant’s experience and perspectives on the effect of FoRSHE-X intervention on their health.
		Self-efficacy	
		Distress Thermometer	
** **		SQoL-F	
**Adoption**	To evaluate the feasibility of digital education, telecoaching, and intervention agents.	Complete response to the questionnaire	Researcher daily memoing
		Facilitators satisfaction	Facilitators’ experience with digital education and telecoaching.
**Implementation**	To evaluate the process of implementation (usability).	Coaching log book	Participants desire and challenges to follow the intervention.
		Proof of telecoaching attendance	
**Maintenance**	To evaluate the intervention sustainability or participants’ involvement over time.	Participant’s diary notes	Participant’s experience and perspectives towards digital education and telecoaching activities.
		Participant’s adherence on telecoaching	
		Follow-up rate	
		Participant retention	

### Study settings

The study will be initiated at the Dharmais National Cancer Center (DNCC) in Jakarta, Indonesia. It is a comprehensive cancer center providing cancer care, education, research, and data in Indonesia. As a national referral hospital, it serves as the central hub for cancer diagnosis, treatment, and management, serving patients from Jakarta and nationwide. DNCC offers chemotherapy in several units, including the Systemic Therapy Unit, One Day Care Unit, and Inpatient Unit, in which the potential participants will be recruited, informed about the study, and signed the research consent. Then, the overall study activities will take place online. Digital assessment forms and educational materials are prepared to be accessed by the participants from their homes.

The core team for this research consists of nurses with expertise in cancer care. The principal investigator is a professor of nursing who will oversee the study and deliver the telecoaching intervention. The research team members include nurses working in academia and at the DNCC. The nurses at DNCC will help provide a list of patients who may be eligible for this study. In addition, a medical oncology consultant will also be involved in the study implementation process.

The protocol of this study has been approved by the Ethics Committee of Nursing Faculty, Universitas Indonesia (Approval number: KET-136/UN2.F12.D1.2.1/PPM.00.02/2023) on 29^th^ May 2023 and the committee of the Medical Research Ethics of the Dharmais Cancer Hospital (Approval number: 259/KEPK/VIII/2023) on 8^th^ August 2023. The ISRCTN registry had reviewed and registered this trial (ISRCTN13311651) on 11^th^ March 2024. Any changes or modifications to the protocol before or during the study data collection will be informed to the ethics committee, research team, and the participants if needed.

The participants’ recruitment will be initiated in October 2023 and is scheduled to be terminated in June 2024. Then, evaluation and data analysis of the study outcomes will be performed from July to September 2024.

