## Abstract

Most Indonesian gynecological cancer survivors have unmet supportive care needs during chemotherapy, which may lower their quality of life and discontinue the treatment. Digital health intervention can address this issue. This pilot investigation aims to (1) examine the feasibility and acceptability of a Fighting on distRess, Self-efficacy, Health Effects, and seXual issues (FoRSHE-X) intervention and (2) evaluate prospectively the impact of the study implementation on the level of distress, self-efficacy, side effects’ knowledge and management, and sexual quality of life using the RE-AIM (Reach Effectiveness, Adoption, Implementation, and Maintenance) framework. This is a non-randomized mixed-methods pilot study. We will recruit women diagnosed with gynecological cancer undergoing chemotherapy to participate in the FoRSHE-X intervention consisting of ten weeks of social media-based education and telecoaching. We will evaluate the primary outcomes of study feasibility and acceptability, and the secondary outcomes of study impacts at three time points with quantitative and qualitative inquiries. We anticipate a minimum of 30 participants to enroll in the study and complete the assessment. We will disseminate results through conferences and peer-reviewed scientific journals. This study will imply whether a definitive trial to evaluate the potential benefits of the FoRSHE-X is viable and how it should proceed. The protocol can aid researchers or nurses in implementing this approach in their study or practice.

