### Sampling

We will recruit participants in the DNCC’s One Day Dare Unit and inpatient units. The eligibility criteria will be (1) female aged 18 years or older, (2) being diagnosed with gynecologic cancer (including cervical, ovarian, uterine, vulvar, vaginal, and fallopian tube cancer), (3) receiving chemotherapy at the DNCC, (4) having a smartphone, (5) willing and physically or cognitively able to participate in the study and follow the study procedures, and (6) being able to communicate in Bahasa Indonesia.

On the other hand, patients diagnosed with severe neurological conditions such as unmanaged mental health diagnosis, current metastases to the brain, delirium, and dementia, as well as those with any prior history of receiving chemotherapy or cancer recurrence, will be excluded because these conditions might confound cognitive functioning [24]. Patients with severe hearing or visual impairment that would prevent them from communicating and using the educational digital material will also be excluded. Another exclusion criterion is patients who are single, divorced, or widowed with no sexual partner.

Thirty participants will be recruited using a convenience sampling technique to enroll in the study. A sample size of 30 participants is considered sufficient for evaluating the feasibility of a clinical trial and providing preliminary estimates of the effect sizes of the study outcomes [24]. Before the data collection, the participants will be provided with an explanation of the study activities and their rights, as detailed in the information sheet. The participants will be able to ask questions about any unclear aspects to the researchers and to participate in this research voluntarily. Subsequently, if a participant agrees to be involved in this study, she will sign the Informed Consent Form prepared by the study team. Meanwhile, the participant can withdraw from the study at any time.

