### Outcomes measures

#### Primary outcomes

The primary outcomes will be assessed at the end of the study period through quantitative and qualitative data collection. The data will cover participant recruitment and retention, the implementation of the intervention, and participant satisfaction.

The research team will maintain a log book to record: (1) recruitment rate: the number of gynecological cancer patients approached to participate in the study, (2) response rate: the number of patients who met the eligibility criteria and signed informed consent, (3) participation rate: the number of participant attendances in social media-based education and telecoaching sessions, (4) facilitators’ satisfaction rate, (5) participants’ satisfaction rate, and (6) attrition rate: the number of participants who received the intervention and were retained in the study until the final follow-up (week 10).

We will carry out a qualitative evaluation to assess (1) intervention adherence, (2) acceptability of the recruitment processes, intervention design and delivery, and outcome measurements, (3) barriers to recruitment and intervention delivery, and (4) participant satisfaction. Qualitative data will be collected through semi-structured interviews with the participants after the study’s completion. An experienced qualitative researcher will conduct the interviews which will be recorded using an audiotape and transcribed by a research assistant. The qualitative data collection will be terminated when the data reaches saturation.

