### Data analyses

Descriptive statistics of participants’ clinical and demographic characteristics and all study outcomes will be reported. The recruitment and retention rates will be computed to determine the feasibility of a full RCT. A future complete RCT will be deemed feasible if the recruitment rate is at least 50% and the retention rate is at least 50%. Response rates to questionnaires, follow-up rates, and intervention adherence rates will also be calculated to provide further evidence for the feasibility of a definitive RCT. For the secondary objective, we will compare the longitudinal quantitative outcomes at three-time points (before, at the middle, and after the interventions) using the paired t-test (for continuous variables) and McNemar’s test (for categorical variables), if the data are normally distributed. The non-normally distributed data will be checked using the Wilcoxon test.

Qualitative data will be analyzed using content analysis by the research team’s qualitative researchers. The team will develop a codebook based on the study objective and framework. The predetermined codes include acceptability, implementation, facilitators, barriers, and satisfaction. A qualitative researcher will code the transcripts once the final codes have been defined and agreed upon. Emerging codes can be added to the codebook during the analysis. After the analysis, a detailed description of the findings will be reported. The qualitative findings will inform the acceptability of the study and the strategies or best practices of the study protocol. All research data will be stored in a non-publicly open repository which can be accessed by the principal researcher only to protect participant confidentiality.

The core team for this research consists of nurses with expertise in cancer care. The principal investigator is a professor of nursing who will oversee the study and deliver the telecoaching intervention. The research team members include nurses working in academia and at the DNCC. The nurses at DNCC will help provide a list of patients who may be eligible. In addition, a medical oncology consultant will also be involved in the study implementation process.

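### The feasibility rule has no time element and no link to the pilot's own target of 30 in its recruitment window, so a pilot well short of target can still be read as supporting the RCT

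*Protocol article*

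**What the plan says.** Four parts of the protocol article bear on this.

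- **Target.** Sampling states: "Thirty participants will be recruited using a convenience sampling technique to enroll in the study". The Abstract goes a little further: "We anticipate a minimum of 30 participants to enroll in the study and complete the assessment".
- **Window.** Study settings says that "recruitment will be initiated in October 2023 and is scheduled to be terminated in June 2024", with evaluation and analysis from July to September 2024.
- **Decision rule.** Data analyses states: "A future complete RCT will be deemed feasible if the recruitment rate is at least 50% and the retention rate is at least 50" per cent. It adds: "Response rates to questionnaires, follow-up rates, and intervention adherence rates will also be calculated to provide further evidence for the feasibility of a definitive RCT". Those further rates have no thresholds.
- **Definitions.** Primary outcomes lists "recruitment rate: the number of gynecological cancer patients approached to participate in the study" and "response rate: the number of patients who met the eligibility criteria and signed informed consent". Both are counts, with neither a denominator nor a period. The other logged items (participation, the two satisfaction rates, attrition) have no accrual period either. Qualitative work will cover "barriers to recruitment and intervention delivery".

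**The concern.** The Design plan asks whether a definitive trial can be conducted, whether to proceed, and how. The Discussion counts participant recruitment as part of feasibility. Recruitment has two separate components: how willing women are to join once approached, and how many suitable women come forward in a given time. A percentage threshold can speak only to the first.

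The second is a real unknown here. Women with any prior chemotherapy, with recurrence, or without a sexual partner are excluded, and recruitment is at one hospital. Sampling is by convenience from lists supplied by nurses, so an acceptance share also depends on whom staff choose to approach. Selective approaching can raise the share without adding a single participant.

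The article fixes a number and a window, which together imply a pace, and then leaves both out of the verdict. What is at stake is a feasible conclusion that carries no information on how many centres or how long a recruitment period the RCT would need.

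**Working it through.** **Inputs from the article.** Target 30 (Sampling). Window October 2023 to June 2024, which is 9 calendar months (Study settings). Rule: recruitment rate at least 50% and retention rate at least 50% (Data analyses). Final follow-up at week 10 (Primary outcomes). The figure of 30 is supported by a citation and not by a calculation, so there is no formula to reproduce.

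**Assumption.** Recruitment rate = consented / approached. The article does not say this, but a bare count of women approached cannot be compared with 50%.

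**Step 1: implied pace.** 30 / 9 = 3.33 women a month. If all week-10 data were wanted by 30 June 2024, enrolment would close ten weeks earlier, on about 21 April. That leaves about 6.7 months from 1 October and a pace of 30 / 6.7 = 4.5 a month. The article does not say which applies. Enrolment on 30 June would put week 10 at about 8 September, inside the analysis period.

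**Step 2: apply the rule to hypothetical pilots.** The first four run over nine months.

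| Enrolled / approached | Recruitment rate | Retained | Retention rate | Share of 30 | Per month | Rule |
|---|---|---|---|---|---|---|
| 20 / 40 | 50% | 10 | 50% | 67% | 2.22 | pass |
| 12 / 15 | 80% | 6 | 50% | 40% | 1.33 | pass |
| 10 / 20 | 50% | 5 | 50% | 33% | 1.11 | pass |
| 5 / 10 | 50% | 3 | 60% | 17% | 0.56 | pass |
| 30 / 70, in two months | 42.9% | any | any | 100% | 15.0 | fail |

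The last row shows the converse: a pilot that fills in two months fails. The rule does not track accrual in either direction.

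**Step 3: would accrual be informative at this size?** Take 12 women in nine months and an exact Poisson 95% interval, assuming a constant rate. The limits for the count are 6.20 and 20.96. Divided by 9, they give 0.7 to 2.3 a month, which excludes the planned 3.3. A pilot of this size can therefore tell a serious shortfall from the planned pace.

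**Step 4: what the pace means for an RCT (illustration only).** Assume two arms, a standardised difference of 0.5, 80% power, two-sided 5% and a single centre; none of these is in the article. The normal approximation gives 62.8 per arm, and 64 with the t correction, so 128 analysed. Enrolment needed is 128 / 0.8 = 160 at 80% retention, or 128 / 0.5 = 256 at the 50% that the rule accepts.

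- At 3.33 a month: 160 / 3.33 = 48 months; 256 / 3.33 = 77 months.
- At 1.33 a month: 160 / 1.33 = 120 months; 256 / 1.33 = 192 months.

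The present rule treats all four as feasible.

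**The case against.** The strongest reply is that the two thresholds are not all the evidence. The number of eligible, consenting women is logged and the window is known, so anyone can divide one by the other. Recruitment difficulties are explored with participants and facilitators, and the article asks how an RCT should proceed as well as whether. This stands in part: the raw material for an accrual figure largely exists, and a shortfall would probably be discussed. But the article states its go rule with thresholds, and nothing on pace or number enrolled enters it. This is a rule fixed badly, not a detail left to a fuller document.

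Second, the share reading is inferred. If the 50% meant the share of the target of 30 reached, 12/30 = 40% would fail. That is fair: the text settles neither reading, and the 12-of-15 example depends on the one chosen. Even so, 15 of 30 would pass on the other reading, and neither reading contains a time unit.

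Third, 30 within the window is the pilot's planning figure, not an RCT requirement. A pilot exactly on pace still implies 48 or 77 months under the illustration above, so a hard gate at 30 would not itself show that an RCT is workable. This also stands. It is why accrual should shape the RCT's centres and duration and not act as an automatic stop.

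A reader might also infer that this hospital will recruit poorly, or could not fill an RCT. The article supports neither. It describes a national referral centre, says only that the study starts there, and never confines the RCT to one site. The pace of 3.3 a month is a plan for a convenience sample and not a measure of capacity.

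**Conclusion.** The concern holds in a limited form. The go rule has no time element and is not tied to the target of 30 or to the October 2023 to June 2024 window. With recruitment rate read as consented over approached, a pilot that enrols 40% of its target (12 of 30, at 1.3 a month against a planned 3.3) meets both thresholds, and so does one that enrols 17%.

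This rests on that reading of an undefined rate and on nine open months; with fewer open months the planned pace is higher. The scenarios show what the rule permits and do not predict poor accrual. The RCT durations depend on an assumed sample size and a single centre and are not figures from the article. The point merits a change because it bears on the pilot's own question and costs little to correct.

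**What to change.** **Primary outcomes.** Define the numerator and denominator of the recruitment rate (for example, women consented over eligible women approached). Log the date of each consent; the article mentions a signed form and a log book but does not say that dates are kept. Add an item such as: *accrual: women enrolled per month of open recruitment, by unit*. State when enrolment closes, given the ten-week follow-up; if it stops at the thirtieth woman, count open months up to that date.

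**Data analyses.** Report accrual with its 95% interval next to the acceptance rate, and compare it with the planned pace: 30 over the months actually open, about 3.3 a month if nine. Add a sentence such as: *if fewer than 30 women are enrolled in the window, the RCT will not be called feasible on the two percentages alone but will be planned with more centres or a longer recruitment window, based on the observed accrual.*

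**Cost.** Wording and one date field; no extra visits or participants. The verdict may become less favourable. If recruitment has begun, the criterion would be added when accrual is partly known, so it must be dated and notified to the ethics committee as an amendment, as Study settings requires for any change, and the report should say when it was added.

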### Sampling

We will recruit participants in the DNCC’s One Day Dare Unit and inpatient units. The eligibility criteria will be (1) female aged 18 years or older, (2) being diagnosed with gynecologic cancer (including cervical, ovarian, uterine, vulvar, vaginal, and fallopian tube cancer), (3) receiving chemotherapy at the DNCC, (4) having a smartphone, (5) willing and physically or cognitively able to participate in the study and follow the study procedures, and (6) being able to communicate in Bahasa Indonesia.

On the other hand, patients diagnosed with severe neurological conditions such as unmanaged mental health diagnosis, current metastases to the brain, delirium, and dementia, as well as those with any prior history of receiving chemotherapy or cancer recurrence, will be excluded because these conditions might confound cognitive functioning [24]. Patients with severe hearing or visual impairment that would prevent them from communicating and using the educational digital material will also be excluded. Another exclusion criterion is patients who are single, divorced, or widowed with no sexual partner.

Thirty participants will be recruited using a convenience sampling technique to enroll in the study. A sample size of 30 participants is considered sufficient for evaluating the feasibility of a clinical trial and providing preliminary estimates of the effect sizes of the study outcomes [24]. Before the data collection, the participants will be provided with an explanation of the study activities and their rights, as detailed in the information sheet. The participants will be able to ask questions about any unclear aspects to the researchers and to participate in this research voluntarily. Subsequently, if a participant agrees to be involved in this study, she will sign the Informed Consent Form prepared by the study team. Meanwhile, the participant can withdraw from the study at any time.

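### The 50% recruitment bar has no stated denominator; because willingness is an eligibility criterion and approach is by convenience, one choice makes the bar uninformative and the other is open to upward bias

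*Protocol article*

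**What the plan says.** All references are to the protocol article.

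- **Eligibility (Sampling).** Inclusion criterion (5) is "willing and physically or cognitively able to participate in the study and follow the study procedures".
- **Sampling method (Sampling).** "Thirty participants will be recruited using a convenience sampling technique to enroll in the study". No order of approach is given.
- **Source of patients (Study settings).** "The nurses at DNCC will help provide a list of patients who may be eligible for this study".
- **Log-book measures (Primary outcomes).** Item (1) is "recruitment rate: the number of gynecological cancer patients approached to participate in the study". Item (2) is "response rate: the number of patients who met the eligibility criteria and signed informed consent". Both are called rates but worded as counts.
- **Reach (Design plan, Table 1).** The quantitative measures include "Acceptance of the research invitation", without a formula.
- **Go rule (Data analyses).** "A future complete RCT will be deemed feasible if the recruitment rate is at least 50% and the retention rate is at least 50" (per cent). The section does not say what is divided by what.

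**The concern.** Reach is tied to the first primary objective, and recruitment is half of the rule for proceeding to an RCT. A percentage bar needs a numerator and a denominator, and the article supplies two counts. The wording of criterion (5) makes the missing denominator matter more than it otherwise would: read literally, a woman who declines fails a criterion and drops out of the eligible group, so the thing to be measured has become an entry condition.

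Counting refusers through the number approached avoids that problem but leaves another. Staff may approach whom they find convenient, and since willingness is a criterion, a woman thought unlikely to agree could be passed over without any breach of the protocol.

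At stake is whether the same recruitment experience is reported as a pass or a fail, and whether the figure carried into planning the RCT reflects the uptake it would meet.

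**Working it through.** **The plan's own figures.** The 30 participants and the 50% bar are stated without a calculation; the sample size rests on a citation ("A sample size of 30 participants is considered sufficient for evaluating the feasibility of a clinical trial"). There is nothing to reproduce, so the check asks what the recruitment rate would be under each possible denominator.

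**Inputs.** From the article: 30 enrolled (Sampling) and the bar of 50% (Data analyses). Assumed, because the article gives no figures: the share *w* of otherwise eligible women who are willing, and the share *e* of women approached who meet every criterion other than willingness. I also assume that every willing woman signs consent.

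**Formulas for 30 enrolled**

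- Otherwise eligible women approached: E = 30 / w
- All women approached: A = E / e
- Rate over all approached: 30 / A = w × e
- Rate over the otherwise eligible: 30 / E = w
- Rate over the eligible, willingness included: 30 / 30 = 100% for every w

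**1. Where the bar falls on the approached denominator.** 30 / A ≥ 0.50 requires A ≤ 30 / 0.50 = 60. The bar is passed with 60 or fewer approached and failed with more.

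**2. The same study under the three denominators**

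| Assumed w | Assumed e | Otherwise eligible | Approached | Over all approached | Over otherwise eligible | Over eligible incl. willing |
|---|---|---|---|---|---|---|
| 0.30 | 1.0 | 100 | 100 | 30% | 30% | 100% |
| 0.40 | 1.0 | 75 | 75 | 40% | 40% | 100% |
| 0.40 | 0.8 | 75 | 93.8 | 32% | 40% | 100% |
| 0.60 | 1.0 | 50 | 50 | 60% | 60% | 100% |
| 0.60 | 0.8 | 50 | 62.5 | 48% | 60% | 100% |

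The last column is 100% throughout an assumed range of w from 20% to 80%. At w = 0.40 the study fails at 30/75 = 40% or passes at 30/30 = 100%, depending only on the denominator. The bottom row shows why the approached rate should not stand alone: it mixes ineligibility with refusal, so 60% uptake can be reported as 48%.

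**3. Convenience approach.** Let the odds of willingness among women approached be OR times the odds among all otherwise eligible women (equivalently, a willing woman is OR times as likely to be approached as an unwilling one). With e = 1:

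observed rate = o / (1 + o), where o = OR × w / (1 − w)

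For w = 0.40, w / (1 − w) = 0.667:

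- OR = 1: o = 0.667, rate 40%
- OR = 1.5: o = 1.00, rate 50%
- OR = 2: o = 1.33, rate 57%
- OR = 3: o = 2.00, rate 67%

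For w = 0.30 and OR = 1.5, 2 and 3, the rates are 39%, 46% and 56%. The odds ratios are illustrations. If approach is unrelated to willingness there is no inflation.

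**4. Precision.** Exact 95% intervals, treating the number approached as fixed, are 37% to 63% for 30/60 and 29% to 52% for 30/75. Even a well-defined rate is a rough guide at this size.

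**The case against.** A reader might infer that the recruitment rate is inflated by construction and can never fail the bar. The documents do not support that. No section names eligible patients as the denominator. The only text attached to the recruitment rate concerns patients approached, and the response item, which combines eligibility with consent, reads naturally as a numerator over that count. On this reading a refuser lowers the rate whether she is labelled ineligible or declined, so the wording of criterion (5) has no effect on it, and 30/75 = 40% fails.

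The article also keeps willingness and consent apart in places. The response item lists eligibility and consent as two conditions, Sampling describes consent as a later step after explanation and questions, and Table 1 counts acceptance of the invitation, which presupposes that some decline. Wording such as that of criterion (5) is conventional. Nothing says that decliners are reclassified and removed from the log.

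Convenience sampling is openly declared and common in small pilots. The nurses' list is of patients who might be eligible, not of those likely to agree. No evidence shows that approach depends on willingness.

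All of this stands against the stronger reading. It does not settle the denominator: a count cannot be compared with 50%, consented over eligible remains open to the analyst because the response item itself names eligibility, and nothing in the stated sampling method guards against selective approach. Nor is this detail that an article merely leaves out: the measures, the criterion, the sampling method and the bar are all stated, and together they do not determine the result.

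**Conclusion.** The point holds in a conditional form. The recruitment half of the go rule depends on a denominator that the article does not fix.

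- **Eligible patients, willingness included, as denominator:** the rate is near 100% at any true uptake, provided that women counted as willing go on to sign, and the bar is uninformative.
- **All approached as denominator:** the bar works, and 30 enrolled fails it once more than 60 are approached. Convenience approach then carries a risk of upward bias of unknown size. A true 40% reaches the bar at an assumed odds ratio of 1.5 and is unchanged at 1.

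It would go too far to say that both rates are certainly inflated or that the bar cannot be tested: the first case rests on a choice that the article does not state, and the second on a selection that it does not document. The log already records patients approached, so an informative rate can be had. This is an inexpensive improvement to a rate that decides whether to proceed, not proof that the feasibility assessment is invalid.

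**What to change.** 1. Remove willingness from criterion (5), keep the ability requirement, and treat willingness as the consent outcome.
2. In Primary outcomes and Data analyses, define the go-rule recruitment rate as consented / all approached. Also report consented / approached who meet all other criteria. Keep decliners in both denominators.
3. Replace convenience sampling with consecutive approach: take the women on the nurses' list in order until 30 consent.
4. Log each listed woman as not eligible, not reached, declined or consented, so that the number listed but not approached can be reported.

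The cost is one phrase in the criteria, one sampling sentence, two rate definitions and a few log-book columns. Staff will have slightly more approach work, and the reported recruitment rate will probably be lower. Consecutive approach does not correct for women who never reach the list. With 30 enrolled the bar remains a descriptive guide, so the rate should be shown with its interval.
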